#### Biochemical assessments

A venous blood sample of 10 ml will be drawn from each participant under aseptic conditions after an overnight fast (12 h). This will be done at the hostel premises, while half of the blood volume will be centrifuged within one hour, and the serum/plasma separated, aliquoted and kept frozen at − 20 °C until further analysis. The remaining blood will also be stored as whole blood. The samples will be analysed as given below at the Faculty of Medicine, University of Colombo, Sri Lanka.*Micronutrients:* Serum Folate, Vitamin D and serum ferritin using the MAGLUMI® chemiluminescence immunoassay (CLIA) and serum calcium level using commercially available kits*Health and immune biomarkers:* Serum lipid profile, FBS, AST, and ALT using commercially available kits, and hsCRP, serum insulin and immune markers (IL-6, IL-10) using the MAGLUMI® chemiluminescence immunoassay (CLIA).

Further, antioxidant capacity will be analysed using colorimetric ABTS method at the Industrial Technology Institute, Sri Lanka [52].

#### Stool sample collection and storage

Samples collected into stool specimen collection containers will be stored at −80℃ at the Faculty of Medicine, University of Colombo, Sri Lanka. The samples will be assessed for metagenomics based on bacterial 16S RNA (V3-V4 region) and fungal ITS1 region using illumina platform [7]. The analysis will be carried out at Credence Genomics (Pvt) Ltd., Sri Lanka by trained analysts.

The collected stool and blood samples will be subjected to bio banking, preserving at −80^0^C for future analysis.

### Statistical analysis

Data will be analysed using the statistical package for the for the Social Sciences (SPSS) version 21.0. The changes in nutritional, health and immune parameters between the baseline (T_0_) and at the end of control phase (T_1_) will be analysed first to identify any significant change with time. The end point of control phase will serve as the pre-intervention point for further assessments. The changes in outcomes between the pre-intervention point (T_1_) and at the end of intervention phase (T_2_) will be analysed to determine any significant effects of *diyabath* consumption on the study group.

Paired t-test will be performed to determine the significance of the mean difference of pre- and post- measurements during the intervention phase. *P* value less than 0.05 is considered statistically significant.$$\begin{aligned} {\mathrm H}_0=\:&\left[\mathrm{Pre}-\mathrm{intervention}\;\mathrm{measurements} -\mathrm{post}\right. \left.-\:\mathrm{intervention}\;\mathrm{measurements}\right]=0 \end{aligned}$$

The same analysis will be performed in relation to the control phase. This evaluation is important to reveal any possible change in parameters that can occur due to seasonal, physiological or climatic changes in individuals.

Further, independent sample t-test will be performed to assess the significance between the intervention and control phases, in relation to the mean change in pre- and post-measurements observed during the intervention and control phases.$$\begin{aligned} {\mathrm H}_0=\:&\left[\mathrm{Mean}\;\mathrm{change}\;\mathrm{in}\;\mathrm{control}\;\mathrm{phase} \right. \left. -\:\mathrm{Mean}\;\mathrm{change}\;\mathrm{in}\;\mathrm{intervention}\;\mathrm{phase}\right]=0 \end{aligned}$$

Bioinformatics analysis of metagenomics of microorganisms evaluated from stool samples will be carried out based on16S amplicon sequence variants (ASVs) model.

Analysis of the effect of diyabath on primary outcomes will be based on modified intention-to-treat (mITT) and per-protocol (PP) principles. The mITT population will include participants who completed the first 15 weeks of the study period which covers the control phase and half of the intervention phase. The PP population will include the participants who completely adhered to the study protocol [53]. Missing data will be adjusted with multiple imputation.

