**Methods:**

This is a single arm, non-randomized controlled trial among 45 women aged 20–35 years, purposively selected from a residential hostel in Colombo District, Sri Lanka. The primary outcomes: gut microbiome composition, nutritional status, and health and immune markers will be assessed before and after a 10-week control phase, during which participants will follow their usual dietary habits (control). In the subsequent 10-week intervention phase, the same participants will consume *diyabath* daily as a pre-breakfast meal (intervention). The *diyabath* will be prepared according to an optimal recipe identified through a comprehensive evaluation of traditional recipes during the intervention development phase. Outcomes will be reassessed immediately and one month after completing the intervention. Changes in outcomes between the control and intervention phases will be compared.

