## Methods

### Study design

This protocol is for a single arm, non-randomized, controlled trial (Fig. 2) reported in accordance with the SPIRIT statement. This design will ensure that factors, such as gut flora, digestion and other physiological variables, which could influence the study results, remain consistent in participants throughout the study period, as the same group of participants will serve as both the control and test groups. This consistency will enable reasonable comparisons with minimum effect due to individual differences. A wash-out period is not considered in the design, as *diyabath* is introduced as the intervention only after the initial control phase.

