## Discussion

There is currently no scientific data available on traditional fermented rice-based pre-breakfast meals like *diyabath*, making it essential to gather traditional knowledge about it from community and indigenous medical practitioners and to scientifically evaluate its properties and functionality, in order to develop interventions that are of practical value in low-resource countries where rice constitutes the staple diet. This methodology could serve as a model to evaluate other indigenous food in the future.

One of the major challenges in interventions based on traditional food is maintaining the consistency in its composition and texture. To address this, the trial plans to strictly adhere to the developed SOP. However, since the fermentation can still vary depending on the environmental conditions such as temperature, especially when conducted domestically, therefore, *diyabath* for the intervention will be prepared in the same place throughout the study. Furthermore, to check whether microbial composition of *diyabath* drastically, samples of *diyabath* provided for the intervention will be analysed randomly during the study.

Previous studies have reported considerable variability over time in the patterns of gut microbiome diversity among individuals undergoing the same food-based intervention [7]. This variability may be due to differences in metabolic conditions, such as inflammation levels. Therefore, using same participants as the test and control groups will minimize the impact of factors such as food preferences, individual metabolism and other physiological variables on the comparisons between test and control groups, revealing the true impact of the intervention on each individual.

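### The plan puts the question of diyabath's effect to the uncontrolled T1 to T2 paired t-test and does not make the planned between-phase comparison the deciding one

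*Protocol article*

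**What the plan says.** The Statistical analysis section of the protocol article sets out three comparisons for the nutritional, health and immune measures.

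1. **T1 to T2.** This change "will be analysed to determine any significant effects of" diyabath. The method is a paired t-test, "performed to determine the significance of the mean difference of pre- and post- measurements during the intervention phase", with the null hypothesis that pre minus post equals zero.
2. **T0 to T1.** "The same analysis will be performed in relation to the control phase", in order to "reveal any possible change in parameters that can occur due to seasonal, physiological or climatic changes in individuals".
3. **Between phases.** An "independent sample t-test will be performed to assess the significance between the intervention and control phases", with the null hypothesis that the mean changes in the two phases are equal.

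The abstract names only the third: "Changes in outcomes between the control and intervention phases will be compared". The Sample size section uses only the first: it takes P1 as the expected percentage at T1 and P2 as the expected percentage at T2. No section ranks the three comparisons or says which one supports a claim that diyabath works.

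**The concern.** A before-after test in one group asks whether the mean moved, not why it moved. The Statistical analysis section itself accepts that outcomes may shift with season, physiology or climate. If they do, the T1 to T2 null hypothesis is false even when diyabath does nothing, and a test at the 5% level no longer has a 5% chance of a false claim about diyabath.

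Using the same women removes stable differences between women. It does not remove calendar time. The trial has one arm and a fixed order, so the control phase is its only protection against time trends, and that protection works only if the control-phase change enters the test that decides the claim. As written, the test given the task of determining the effect leaves it out.

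**Working it through.** **The plan's own figure.** Inputs from the Sample size section: p1 = 31, p2 = 73, f = 7.9, design effect 2, non-response 25%.

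- N = {31×69 + 73×27} × 7.9 / (73−31)² = (2139 + 1971) × 7.9 / 1764 = 18.41, as stated.
- × 2 = 36.82, as stated.
- × 1.25 = 46.03, against the stated 45. The small difference does not matter here.

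The calculation contains T1 and T2 only. Nothing in it refers to the T0 to T1 change.

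**False-positive rate of the T1 to T2 test under drift.** The article gives no drift and no SD of change, so drift d is an assumption, in SDs of the within-woman 10-week change. The test is taken as two-sided at 0.05. With no effect of diyabath, the paired t statistic follows a noncentral t distribution with n−1 degrees of freedom and noncentrality d√n. For example, at n = 45 and d = 0.3 the noncentrality is 0.3 × 6.708 = 2.01, against a critical value of 2.015, so rejection is close to a coin toss.

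| Assumed drift d | n = 45 | n = 36 |
|---|---|---|
| 0 | 5% | 5% |
| 0.1 | 10% | 9% |
| 0.2 | 26% | 21% |
| 0.3 | 50% | 42% |
| 0.5 | 91% | 83% |

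**The per-woman contrast with equal drift in both phases.** The contrast (T2−T1)−(T1−T0) = T2 − 2·T1 + T0 cancels a drift that is the same in each phase. In 40,000 simulated trials with independent visit errors and no effect of diyabath, the paired test of this contrast rejected in about 5% at every drift tried (0 to 0.5 SD, n = 36 and n = 45). The independent-sample version in the plan rejected in about 11%, because it ignores that the same women supply both changes and share T1. That is a separate fault.

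**The contrast with drift in the intervention phase only.** Nothing cancels. At n = 45 the contrast rejects in about 21% of trials at 0.3 SD and 47% at 0.5 SD, against 50% and 91% for T1 to T2.

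**Precision.** With common variance σ² and equal correlation ρ between visits:

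- Var(T2−T1) = (1+1)σ²(1−ρ) = 2σ²(1−ρ)
- Var(T2−2·T1+T0) = (1+4+1)σ²(1−ρ) = 6σ²(1−ρ)

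The ratio is 3. An effect with 80% power on T1 to T2 has a standardised distance of 1.96 + 0.84 = 2.80. On the contrast this becomes 2.80/√3 = 1.62, and power is Φ(1.62 − 1.96), about 37%. The exact t calculation gives 37% at n = 36 and at n = 45.

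**The case against.** The strongest reply is that the plan does not ignore its control. It tests the control phase for change over time, gives the reason for doing so, and sets up a formal between-phase test with its own null hypothesis. The abstract names only that comparison. All of this stands. A reader might infer that the control phase is discarded and that every drift will be credited to diyabath. The article does not support that reading, because no section says that the claim rests on T1 to T2 alone. What survives is narrower: the effect question is explicitly given to T1 to T2, and the between-phase test is not made decisive.

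A reader might also infer that an effect will be declared when the intervention phase is significant and the control phase is not. No section states such a rule, so no error rate for it is charged against the plan.

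Two other statements may look like support for a before-after reading: that influencing factors "remain consistent in participants throughout the study period" (Study design), and that the approach succeeds in "revealing the true impact of the intervention on each individual" (Discussion). Both come from sentences about using the same women as control and test groups, so they point towards the controlled comparison.

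It can also be said that ranking tests is commonly left to an analysis plan, which is not shown. That would answer mere silence. Here the article is not silent: it says which change determines the effect, and that change is the uncontrolled one.

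Finally, the remedy is neither complete nor free. It leaves in place any drift specific to the second phase, and it costs power. Both points stand and belong in the fix.

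**Conclusion.** The concern holds in this form: the article gives the question of diyabath's effect to an uncontrolled before-after test, sizes the trial on it, and leaves the planned between-phase comparison without deciding status. Followed as written, the plan would allow a significant T1 to T2 result to be reported as an effect of diyabath even if the between-phase comparison showed none.

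At n = 45 the chance of such a T1 to T2 result with no effect is 26%, 50% or 91% for drifts of 0.2, 0.3 or 0.5 SD of change. These figures depend on the assumed drift. With no drift the rate is the nominal 5%, and the documents do not show that drift will occur, only that the authors regard it as possible. The 5% rate of the per-woman contrast assumes equal drift in both phases. The threefold variance assumes equal correlation between visits.

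**What to change.** In Statistical analysis, state that an effect of diyabath will be claimed only from the per-woman contrast (T2−T1)−(T1−T0), tested as a paired (one-sample) difference. Report the T0 to T1 and T1 to T2 changes as estimates with confidence intervals, without using either as a test of effect. Show T2 to T3 as supportive, since T3 is already scheduled.

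Add a limitation: the contrast removes only drift common to both phases. Change specific to the second 10 weeks stays confounded with diyabath because the control phase always comes first. So does the extra attention in that phase, namely the morning SMS to attend breakfast and the investigator observing the meal.

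In Sample size, state that the calculation and its 80% power apply to T1 versus T2 and not to the contrast.

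**Cost.** No new data or visits are needed, but this is more than a change of wording. With equal correlations the deciding contrast has three times the variance, and an effect with 80% power before-after has about 37% power on it. The sponsor should either accept and state that precision or revisit the sample size.

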**Fig. 3 Fig3:**
[figure not shown]
Time structure of the trial

Primary outcomes of the study include changes in the following parameters:*Host gut microbiome composition:* Evaluated using percentage abundance of probiotic strains (i.e. *Lactobacillus* spp, *Bifidobacterium* spp) and other beneficial microorganisms (i.e. *Oscilllospira*, *Akkermansia muciniphila*), alpha-diversity index and firmicutes-to-bacteroidetes ratio (F/B). Diversity index reveals the change in the gut microbiome composition and is important to have a balanced ratio between the most common two phyla (Firmicutes and Bacteroidetes F/B) for homeostasis of the gut [38]. Gut microbiota is directly responsible to develop digestive, immunological and metabolic functions in host [39, 40].*Nutritional status and health parameters*: Evaluated by serum micronutrients and serum ferritin*Health biomarkers*: Assessed by lipid profile, high-sensitivity C-reactive protein (hsCRP), fasting blood sugar (FBS), aspartate aminotransferase (AST), alanine aminotransferase (ALT) and serum insulin*Immune markers:* Evaluated by analysing interleukin-6 (IL-6), IL-10 and cytokines

Each participant is expected to improve these parameters to either reach a healthy limit or a healthier end if already in the healthy limit.

Secondary outcomes of the study include:*Antioxidant capacity:* An increase in total antioxidant capacity in serum after consumption of an antioxidant rich food indicates absorption of antioxidants from the food and an enhanced in vivo defence status against oxidative stress [41].*Anthropometry:* Measured as waist circumference, hip circumference and BMI

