### Sample size

The study is designed to detect a significant difference in the pre- and post-intervention time points for a given dichotomous variable [42, 43].$$\mathrm N=\left\{{\mathrm p}_1\;\left(100-{\mathrm p}_1\right)+{\mathrm p}_2\;\left(100-{\mathrm p}_2\right)\right\}\times{\mathrm f}_{\left(\mathrm\alpha,\mathrm\beta\right)}/\left({\mathrm p}_1-{\mathrm p}_2\right)^2$$

Where;$$\mathrm{N}=\text{Minimum sample size required for each group}$$$$\begin{aligned} \alpha=\:&\text{The level of significance used for detecting} \\& \text{an intervention difference}\:(0.05) \end{aligned}$$$$\begin{aligned} 1- \beta=\:&\text{The degree of certainty (power) that the difference p1-p2}, \\&\text{if present would be detected, often set at 0.8 (0.2)} \end{aligned}$$

$$f=\text{A function of}\ \alpha\ \mathrm{and}\ \beta\ \mathrm{when}\ \alpha\ \text{is 0.05 and}\ \beta\ \text{is 0.02 (7.9)}$$
$$\begin{aligned} \mathrm{P}_1=\:&\text{Expected percentage of an outcome variable}\\& \text{at the baseline of the intervention} \end{aligned}$$
$$\begin{aligned} \mathrm{P}_2=\:&\text{Expected percentage of an outcome variable} \\&\text{at the end of intervention} \end{aligned}$$

Previous interventional studies on fermented food have shown that host nutritional status, health and immune parameters are predominantly affected by the change in host gut microbiome [42–45]. Therefore, change of gut microbiome composition was used for sample size calculation. Previous studies have used the percentage presence of selected taxonomic groups of microbiota to interpret the gut microbiome changes [7, 46, 47]. Therefore, P1 and P2 in this study were derived based on a 17-week randomized controlled intervention study (*n* = 18, healthy adults) on high fiber food-based diet where percentage presence of *Oscillospira* at baseline was 31% and at the end of the intervention was 73% [7].

Therefore;

P_1_ = Expected percentage presence of Oscillospira at T_1_ = 31% [7] P_2_ = Expected percentage presence of Oscillospira at T_2_ = 73% [7]

The sample size obtained (*n* = 18.41) was corrected to account for design effect due to clustering (d). In most interventional studies, the maximum d has been reported as 2, and therefore the design effect was considered as 2 for this trial [48, 49]. Therefore, after correction, the sample size was 36.82. With another 25% non-response added, the final sample size was 45 participants.

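### The only tests named are t-tests on mean differences, with no transformation and no paired binary test, although the primary outcomes include a ratio, skewed markers and a genus planned as mostly absent at T1

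*Protocol article*

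**What the plan says.** The Statistical analysis section names two inferential procedures.

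- Within the intervention phase (T1 to T2): "Paired t-test will be performed to determine the significance of the mean difference of pre- and post- measurements during the intervention phase". For T0 to T1, "The same analysis will be performed in relation to the control phase".
- Between phases: "independent sample t-test will be performed to assess the significance between the intervention and control phases", applied to the mean change in each phase.

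Both null hypotheses are written as a difference of measurements, or of mean changes, equal to zero. The section mentions no transformation, distribution check, rank test or test for paired proportions, and limits neither t-test to a subset of outcomes. The one sentence specific to the microbiome, "Bioinformatics analysis of metagenomics of microorganisms evaluated from stool samples will be carried out based on16S amplicon sequence variants (ASVs) model", describes how sequences are turned into features. It is not a test.

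The Outcomes section makes these primary, among others: percentage abundance of named taxa including *Oscillospira*, "alpha-diversity index and firmicutes-to-bacteroidetes ratio (F/B"), serum ferritin, hsCRP, serum insulin, IL-6 and IL-10.

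The Sample size section plans for a dichotomous variable, the presence of *Oscillospira*. It takes this from a cited study in which presence "at baseline was 31% and at the end of the intervention was 73" per cent.

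**The concern.** A test on the arithmetic mean difference suits outcomes whose changes are roughly symmetric. Three groups of primary outcomes here are doubtful candidates.

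1. **F/B.** A t-test on a ratio depends on which phylum is the numerator. On the log scale, inverting the ratio only changes the sign.
2. **Positive, typically right-skewed markers** (hsCRP, IL-6, IL-10, insulin, ferritin). A few women with high values can dominate the mean change and its standard error.
3. ***Oscillospira* abundance.** If the genus is absent in most women at T1, most T1 values are zero, and the mean change mixes appearance of the genus with its amount.

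In addition, the binary endpoint that justifies the sample size has no corresponding test. With at most 45 women, what is at stake is efficiency, and estimates that rest on a few participants.

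**Working it through.** **The plan's own figure.** With p1 = 31, p2 = 73 and f = 7.9 (Sample size section):

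N = {31 × 69 + 73 × 27} × 7.9 / (73 − 31)² = (2139 + 1971) × 7.9 / 1764 = 18.41.

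Doubled for the design effect this is 36.8, and × 1.25 it is 46.0, against 45 in the article. The plan is thus sized on a binary outcome, and its figures imply 100 − 31 = 69% of women without the genus at T1.

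**Skewed positive outcomes.** The article gives no SD, skewness or correlation, so these inputs are assumptions: lognormal values, the same 30% fall in every woman (ratio 0.7), n = 45, two-sided 0.05.

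On the log scale the paired t-test has SD of differences = s × √(2(1 − ρ)) and non-centrality |ln 0.7| × √45 / SD. With ρ = 0.7:

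- s = 0.8: SD = 0.8 × √0.6 = 0.620; 0.357 × 6.708 / 0.620 = 3.86; power about 97%.
- s = 1.0: SD = 0.775; non-centrality 3.09; power about 86%.
- s = 1.2: SD = 0.930; non-centrality 2.57; power about 71%.

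The raw-scale power comes from simulation of the same model (20,000 trials per setting):

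| Correlation | Log-SD | Raw scale | Log scale |
|---|---|---|---|
| 0.7 | 0.8 | 84–85% | 97% |
| 0.7 | 1.0 | 58% | 86% |
| 0.7 | 1.2 | 36% | 71% |
| 0.5 | 0.5 | 99% | 99.7% |
| 0.5 | 0.8 | 67% | 83% |
| 0.5 | 1.0 | 42% | 65% |
| 0.5 | 1.2 | 25% | 50% |

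The log-SD 0.5 row is close to the ceiling. When the effect is instead set so that the log analysis has about 80% power (n = 45), the raw test has about 77% at log-SD 0.3, 72–73% at 0.5, 61–63% at 0.8, 51–55% at 1.0 and 39–43% at 1.3. The loss is therefore about 1 to 8 points at log-SD 0.5 or below and 17 points or more from 0.8 upwards.

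With no true change, the raw paired t-test rejected in about 3.5% to 5% of trials.

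***Oscillospira*.** Presence 31% at T1 and 73% at T2, n = 45, lognormal amount when present with correlation 0.5. In each range the lower figure takes presence at the two visits as independent and the higher as nested:

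| Log-SD of amount | t-test on abundance | Wilcoxon on abundance | Exact McNemar on presence |
|---|---|---|---|
| 0.5 | 93–99% | 95–99% | 97–100% |
| 0.8 | 76–87% | 88–96% | 98–100% |
| 1.0 | 64–74% | 86–93% | 97–100% |
| 1.5 | 36–40% | 82–87% | 97–100% |

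At the planned rates, the test that matches the sizing endpoint keeps its power however variable the amount is. The t-test on abundance does not.

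**F/B.** In the lognormal model above, raw t-tests on F/B and on B/F gave different significance verdicts in 22–33% of trials at log-SD 0.8 and about 40% at 1.0, but in 2% or fewer at 0.5.

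**The case against.** **Raw scale is inferred.** The article never says untransformed, and a paired t-test on logs is still a paired t-test, so a fuller plan could supply the scale. This stands as a limit on wording. However, the null hypotheses are written on measurements, nothing is exempted, and no paired binary test is named for the endpoint that sizes the trial. That last gap is a mismatch within the article, not a detail left for later.

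**The power loss is assumed.** This is correct. The log-SDs are not from the documents, and exactly lognormal data with a uniform proportional fall favour logs. The Outcomes section expects women outside a healthy limit to move towards it, so response may concentrate in those with high values. If only the top baseline quarter halves (n = 45, correlation 0.7), raw v log power is 57% v 54%, 38% v 32% and 29% v 23% at log-SD 0.5, 0.8 and 1.0. At correlation 0.5 the two are within about 3 points. The log scale then has no advantage, though this scenario is also an assumption.

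**Many zeros.** A reader might infer that all the listed taxa are mostly absent. The article gives a presence rate only for *Oscillospira*, taken from one cited study of 18 adults, and its Discussion describes that genus as regularly found in 16S surveys. The zeros argument is confined to *Oscillospira*, and to the planning figures being right.

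**F/B orientation.** The article fixes which phylum is on top, so no one is choosing between two answers. What remains is that the result depends on a convention, which the log-ratio avoids.

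**A new endpoint.** Presence is not a listed outcome, so McNemar's test adds one. That is so, but the sample size already rests on it.

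**Conclusion.** The concern holds as a matter of efficiency and of matching the tests to the outcomes. The named t-tests suit the F/B ratio, the skewed markers and *Oscillospira* abundance poorly if these are as variable as log-SD 0.8 or more. The loss is then roughly 12 to 35 points in the uniform 30% fall setting with correlation 0.7. It is small, about 1 to 8 points, at log-SD 0.5 or below. The documents do not say which case applies.

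A reader might infer that the paired t-tests are invalid or that much of the power is certainly lost. Neither follows: type I error of the paired t-test is about 5% or less, and the loss depends on assumed spread, correlation and a proportional effect. Nothing here tells against the t-test for outcomes such as serum calcium or BMI.

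The absence of a paired test for the presence endpoint needs no assumption; it follows from reading the Sample size and Statistical analysis sections together. This is a cheap improvement that should be made.

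**What to change.** Prespecify, before outcome data are examined:

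1. F/B, hsCRP, IL-6, IL-10, insulin and ferritin are log-transformed before the within-phase paired t-tests and reported as ratios of geometric means with confidence intervals.
2. For the same outcomes the control v intervention comparison is made within woman: (log T2 − log T1) − (log T1 − log T0), tested against zero. Log-transforming while keeping the independent-samples test would not be enough, because the two changes come from the same women and share T1. In simulation (n = 45, correlation 0.6) that test had a type I error of about 11% on either scale, against about 5% within woman.
3. *Oscillospira* presence at T1 v T2 is tested with McNemar's test, to match the sample-size basis, with the Wilcoxon signed-rank test on its abundance as support.
4. The t-test is kept for the other outcomes.

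The cost is a short paragraph of analysis text. No new data or visits are needed, and the methods run in the SPSS package already named. The downsides are small: effects are read as percentage changes instead of raw units, one presence outcome is added, and the log scale gains nothing if only women with high baseline values respond.

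### The control-versus-intervention comparison uses an independent-samples t-test on paired change scores that share T1, so its 5% level is not controlled

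*Protocol article*

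**What the plan says.** The Study design section describes one group of women followed through a control phase and then an intervention phase: "the same group of participants will serve as both the control and test groups". The Implementation section repeats that the same participants take part in both phases.

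The Statistical analysis section fixes the role of the middle visit: "The end point of control phase will serve as the pre-intervention point for further assessments". The control-phase change is therefore T1 − T0 and the intervention-phase change is T2 − T1.

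The same section plans three kinds of test:

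- a paired t-test of T1 against T2, within the intervention phase;
- the same paired test of T0 against T1, within the control phase;
- for the comparison between phases, an "independent sample t-test will be performed to assess the significance between the intervention and control phases", applied "in relation to the mean change in pre- and post-measurements observed during the intervention and control phases". The null hypothesis is that the two mean changes are equal.

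The significance rule is that a P "value less than 0.05 is considered statistically significant". Whether tests are one- or two-sided is not stated.

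**The concern.** An independent-samples t-test is valid when the two sets of observations come from unrelated people. Here each woman supplies one value to each set, and the two values are built from an overlapping measurement. A chance high reading at T1 raises her control-phase change and lowers her intervention-phase change by the same amount. This tends to make the two changes negatively correlated. Ignoring pairing usually costs only power. With negative correlation it does the reverse: the standard error comes out too small.

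The within-phase tests are correctly paired, so the between-phase choice is also out of line with the rest of the plan. It matters because this is the only formal test that sets one phase against the other. The paired T1–T2 test cannot by itself separate diyabath from the seasonal, physiological or climatic drift that the protocol says it wants to detect. The abstract also promises a comparison of changes between the phases.

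**Working it through.** **Inputs.** From the protocol: the test, the shared T1, the single group of women and the 0.05 level (two-sided assumed). The sample size is 45 ("With another 25% non-response added, the final sample size was 45 participants"), from 36.82 before non-response, so n = 36 and n = 45 were used in simulation. The protocol gives no SD or between-visit correlation for any outcome, so every covariance structure below is an assumption.

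**Formula.** Let D1 = T1 − T0 and D2 = T2 − T1, with equal variance V and correlation r.

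- Variance of the difference in means that the independent test assumes: 2V/n.
- True variance: 2V(1 − r)/n.
- Actual two-sided level: 2·[1 − Φ(1.96/√(1 − r))].

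At r = 0 this returns the plan's nominal figure, 2·[1 − Φ(1.96)] = 5%.

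**Equal variances and equal correlations ρ at the three visits (variance s²).**

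- Var(D1) = Var(D2) = 2(1 − ρ)s².
- Cov(D1, D2) = (ρ − 1 − ρ + ρ)s² = −(1 − ρ)s².
- r = −0.5 whatever ρ is.
- True Var(D2 − D1) = 6(1 − ρ)s², against 4(1 − ρ)s² assumed: a ratio of 1.5.
- Assumed SE / true SE = 1/√1.5 = 0.82, so the SE is understated by 18%.
- Level = 2·[1 − Φ(1.96/√1.5)] = 10.95%.

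**Correlation decaying with time (AR(1)).** Cov(D1, D2) = (ρ − 1 − ρ² + ρ)s² = −(1 − ρ)²s², so r = −(1 − ρ)/2.

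**Women with persistent differences in trend (random slopes, independent visit errors).** r = (slope variance − error variance)/(slope variance + 2 × error variance), with slope variance per 10-week phase. This is positive only if slope variance exceeds single-visit error variance.

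**Results.** Simulated values are from normal data, 60,000 replicates per scenario, over n = 36 and n = 45.

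| Assumed structure | r | Independent test, formula | Independent test, simulated |
|---|---|---|---|
| Equal variances and correlations | −0.50 | 10.95% | 10.8–11.2% |
| AR(1), ρ = 0.2 | −0.40 | 9.8% | 9.7% |
| AR(1), ρ = 0.5 | −0.25 | 8.0% | 7.8–8.0% |
| AR(1), ρ = 0.8 | −0.10 | 6.2% | 6.0–6.1% |
| AR(1), ρ = 0.9 | −0.05 | 5.6% | about 5.5% |
| Residual variance at T1 twice that at T0 and T2 | −0.67 | 12.9% | 12.9–13.0% |
| Random slopes, slope variance = error variance | 0 | 5.0% | 4.8–5.1% |
| Random slopes, slope variance = 2 × error variance | +0.25 | 2.4% | 2.3–2.4% |

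A paired t-test on the same simulated data gave 4.8% to 5.1% in every scenario of the 60,000-replicate runs.

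**The case against.** Three stronger readings are tempting, and the document supports none of them.

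- **That the true type I error is 11%.** A reader might infer this from the shared T1 alone. It follows only if the three visits have equal variances and equal correlations, which the protocol does not say. Under AR(1) decay the figure is lower throughout. The primary outcomes range from taxon abundance to ferritin, lipids and cytokines, so one rate is unlikely to fit them all.
- **That the test is always anti-conservative.** Negative correlation is the likelier case, but it is not guaranteed. If women differ persistently in trend over the 20 weeks by enough to outweigh visit-to-visit error, the changes become positively correlated. The test is then conservative and loses power.
- **That the trial's claim of a diyabath effect rests on this test alone.** The Statistical analysis section assigns the determination of diyabath effects to the T1–T2 change, tested with a correctly paired t-test, and adds the between-phase test afterwards. The control phase is also examined by its own paired test. What can be said is that this is the only formal test between phases.

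These objections limit the size, direction and reach of the point. They do not rescue the test: it holds its level only if the two changes happen to be uncorrelated, and nothing else in the protocol corrects it. Nor is this a detail left to an analysis plan that is not shown, because the protocol names the test.

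**Conclusion.** The point stands as an error in the test named. Independence is false by design, so the standard error, confidence interval and p-value of the between-phase comparison are wrong unless r = 0.

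The size depends on the covariance structure assumed. The reasonable default of equal variances and correlations gives about 11%, AR(1) decay about 5.5% to 10%, and extra variability at T1 nearly 13%. Positively correlated changes take the level below 5%. All figures assume two-sided testing of a single outcome and equal variances of the two changes. They say nothing about multiplicity across the many primary outcomes.

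The test should be corrected before analysis, since the remedy does not depend on which structure holds.

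**What to change.** In the Statistical analysis section, replace the independent-samples t-test with a paired (one-sample) t-test on each woman's (T2 − T1) − (T1 − T0) = T2 − 2·T1 + T0. The same contrast in a repeated-measures mixed model would also serve. Report the estimate with its confidence interval.

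The stated null hypothesis is unchanged. With complete data so is the estimated mean difference; only the standard error and degrees of freedom change (n − 1 in place of 2n − 2, so 44 in place of 88 with 45 women).

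The cost is one sentence, notified as an amendment by the route the protocol already describes. No new data are needed and the planned software can run the test. The downside for the sponsor is that p-values will usually be less favourable.

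A separate suggestion, which does not follow from the pairing error, is to base any claim of a diyabath effect on this contrast instead of on the T1–T2 test. That would change which analysis decides the trial and should be weighed on its own merits.
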